Study design and the potential for confounding : For the control of confounding, we apply randomization at all levels (for the selection of villages and participants and for the allocation of the intervention). Additionally, we have matched villages on the pre-intervention outcome (diarrhea rate) as suggested by one of the reviewers. These two strategies (randomization and matching) are the most effective ways to reduce the variance of our effect estimate and to remove the potential bias due to confounding. In studying the effect of our intervention, confounding could result, as noted by the reviewer, if we differentially assigned treatment to those villages with either higher or lower inherent rates of diarrhea. However, by matching the villages on the baseline incidence of diarrhea the potential for confounding by differential initial conditions is greatly reduced. In further response to the reviewer, we now will further reduce the potential for mismatching villages by matching them on the basis of an estimate of diarrhea rates for eight weeks (previously based on a single 7 day recall diary) (Section D.6.b.). We will apply our newly adapted and pretested daily morbidity diaries combined with weekly home visits. This will reduce any misclassification bias in the pairing of villages prior to random assignment of the intervention. Based on our own experience in Bangladesh and Bolivia (Appendix F and F2) and that of others (Samanta and Van Wijk 1998), we will assess village characteristics that could be related to compliance by recording factors such as existing collective community efforts (e.g. commitments to community development, income generating projects, community banking accounts, cultural factors), to adjust for them in the analysis stage.

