High efficacy (i.e. the desired result of an intervention under ideal conditions) does not necessarily imply high effectiveness (intended benefit observed in "real world" situations), and there is a need to examine closely the steps that lead to effectiveness in the community. It is crucial to assess how much of the efficacy of SODIS established in previous experimental studies and limited field trials will be retained as effectiveness in the real world. The findings of the proposed trial will influence decisions regarding the extent and method of future dissemination of SODIS. This evaluation is timely since plans for large scale implementation of the methodology are being readied in Bolivia (Appendix C) or are now considered by major donors such as UNICEF in Bangladesh or ministries of health, such as the government of Bangladesh in the Bangladesh Arsenic Mitigation Water Supply Project (BAMWSP)(The World Bank 1998).

We propose to evaluate SODIS through a cluster-randomized, controlled trial in the Cochabamba area of Bolivia. The trial will be conducted in 22 villages in which the families of 30 children under the age of five years will be enrolled in each village. Both the villages and the children within them will be randomly selected from census data. The annual incidence of diarrhea will be measured in the 22 villages (11 pairs) where the SODIS technique will be introduced. Daily measurements (recorded each week) of diarrheal episodes will be made by community-based field staff. Analysis will be conducted with mixed effects models adjusting for the clustered nature of the data. In addition to the measurement of the incidence of disease, we will also collect specimens of stool and home drinking water for extensive measures of pathogen occurrence as was done in our recent pilot studies in Mizque. In particular, our estimates of viral waterborne diarrheal diseases in this setting will represent new information since viral disease occurrence has received little attention. The data will allow us to estimate the relative contributions of specific viral, bacterial, and parasitic pathogens in the etiology of diarrheal disease in this community-based setting. A trial of this kind has not been conducted previously in Bolivia or Latin America. This distinguishes our study from the few prior local hospital-based studies on the etiology of diarrheal disease (Ise et al. 1994, Lopez et al. 1989, Townes et al. 1997, Utsunomiya et al. 1995).

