#### **D.6.b. Baseline morbidity surveys in the trial villages to estimate the period prevalence of diarrheal episodes in children <5 years and to facilitate randomization of communities**

At the beginning of the study, a prospective eight week survey among households with children <5 years will be conducted in the 22 villages to estimate the proportion (period prevalence) of child diarrheal illness. The usually short duration of a diarrheal episode and the short incubation period for a new episode will allow us to estimate the incidence density of child diarrhea in each cluster (i.e. village-cluster incidence rate) at baseline. The main purpose of obtaining a prevalence estimate is to facilitate matching of study sites according to the occurrence of reported diarrhea in children. This change (previously a 7 day cross-sectional survey but now an eight week longitudinal measurement) was done in order to address a comment in the prior review about improving our strategy to minimize possible differences in confounding factors between villages at baseline. Sites ranked by eight week baseline diarrhea rates are then grouped in pairs and the introduction of the SODIS intervention is randomly allocated to one of them. Thus, 11 sites receive the intervention, 11 other sites serve as controls. This high level randomization of the village-clusters to the SODIS intervention is the single most effective strategy to limit bias in the estimation of the intervention effect (Murray 1998) (cf. also Section D.7.). PCI will adapt to the random allocation of the SODIS intervention and will start activities in the villages of the intervention arm after our baseline survey has been completed.

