## D.8. Sample size calculation

Sample size calculations were designed for the trial to detect a 33% absolute reduction in the annual diarrheal incidence rate in children below the age of 5 in SODIS users compared to non-users. We consider a reduction of the annual incidence of 5 to 3.33 episodes per child <5 as of significant public health importance (Bern et al. 1992). This absolute rate reduction (1.67 episodes/child/year) is even lower than what was found in the Kenyan SODIS trials (2.1 epi/ch/yr)(Conroy et al. 1999). Conroy observed 2546 diarrhoeal episodes among a total of 4382 fortnight observation periods (58.1%) in the control group (172 children). A total of 2210 episodes among 4323 observations (48.8%) were found in the intervention group (174 children) resulting in their report of a 9.3% reduction of diarrhoea in children below 6 years. By considering 26 repeated measurements of fortnight periods an approximation of the annual incidence, the Conroy findings suggest an average annual reduction of 2.1 episodes/child/year for a child in the control *versus* intervention group (14.6 *versus* 12.7 epi/ch/yr). The magnitude of diarrhea reduction we have powered the study to detect compares favorably to the achievements of other well designed interventions that influenced national diarrheal disease control programs elsewhere in developing countries (Huttly et al. 1997, Stanton and Clemens 1987).

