| 50%                                     | (2.5 episodes)  | 3.4                                       | 4.5      | 6.5      |

**Design effect:** Ignoring clustering in this trial would turn the trial design into that of a classical clinical trial with individual randomization. The required sample size in terms of person-years of observation (y) is calculated as,

$$y = (z_{a/2} + z_B)^2 \times (R_0 + R_1) / (R_0 - R_1)^2, \text{ and}$$

would result in 23.6 year of person-time of observation in each cluster and in a design effect of ~2.4. (23.6/10)

From those calculations we conclude the following:

**Number of clusters and subjects per cluster:** We assume that the incidence rate of diarrhea in the control villages remains constant at 5 episodes/child/year and that we require 80% power ( $z_a = 0.84$ ) of detecting a significant difference ( $p < 0.05$ ;  $z_{a/2} = 1.96$ ) if the intervention reduces diarrheal incidence by 33%. We will achieve a minimum of 10 person-years of observation in each cluster, which amounts to 10 subjects per cluster observed for the duration of 12 months. Finally, considering a conservative between-cluster variation ( $k=0.2$ ) we would need 9 villages each in the intervention and control group. Based on previous experience in our Bangladesh trial (Hobbins et al. 2000a) we consider a drop out rate of one to two villages per study group and thus adjust final sample size to 22 villages (clusters); 11 in each treatment arm.

Finally, we have included 30 children in each village with the following justification:

i.) few marginal costs arise in investigating more children in each village;

- ii.) this allows us to compensate for loss of follow up of individuals;
- iii.) the study is powered to maintain its ability to detect even a 16% reduction of diarrheal incidence from 5 to 4.2 episodes at a between cluster variation of  $k=0.12$  (cf. Table 2. detailed Calculations not shown).

Thus, overall 660 households, 30 in each of the 22 villages and each with an index child under the age of 5 years enrolled in the trial will be participating in the study.

The following additional information on different parameters was considered in the sample size calculations above:

1. About 15% of the rural population in the study area are children under 5 years.(Centro Desarrollo Agropec., 1994).

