## D.9. Data management and statistical analysis

Descriptive data analysis will be performed and selected demographic and environmental characteristics such age, sex, tribe/religion, household size, socio-economic/educational status, and the availability of water sources will be presented to indicate the effects of randomization and comparability of the intervention groups.

Comparison of rates: Cluster level incidence rates are used as the unit of analysis to compare incidence rates between intervention and control groups. Given the cluster size exceeding  $N=10$  Pearson  $\chi^2$  test can be used to compare cluster or group level incidence rates (Donner and Klar 1994). The calculations of Pearson  $\chi^2$  accounts for the degree of intracluster correlation and the variance inflation due to clustering (Klar et al. 1995).

Bias and Confounding: Randomization procedures throughout the hierarchical structure of this cluster-randomized trial should make intervention groups comparable at baseline at cluster- and village level. Any bias resulting from incomplete randomization or from monitoring specific village factors that relate to compliance as well as unpredictable outside factors (e.g. media) will be dealt with in the analysis.

Evaluation of effect modification will be achieved by including multiplicative interaction terms in a generalization of Poisson regression analysis adapted for the residual correlation of the total number of diarrheal episodes among children in the same cluster (see details below). The effects of well known factors that act as effect modifier such as the presence /absence of sanitary facilities in the compound, or previous exposure to health education will be considered. Preliminary assessment of interaction will be done by stratification and decision will subsequently be made whether to include interaction terms as indicators in the Poisson regression analysis.

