Multivariate statistics: Simple comparisons of rates will be done using software that is designed to accommodate the complexity of a cluster randomization design (SUDAAN). Simple Poisson regression cannot be used to make inferences about the effect of treatment in cluster randomization trials since it is constructed on the assumption that the conditional responses of individuals are statistically independent. An extension of the Poisson regression, generalized estimation equation approach (GEE) will be employed (Liang and Zeger 1986). For these regressions, the number of episodes of diarrhea for each child will be the outcome and, although we will report the inference based on robust estimates of the variance, we will assume the correlation within a cluster to be compound symmetry in the estimation procedure. We can possibly reduce the variance of the estimate of the treatment effect by adjusting for both baseline risk factors measured at either cluster level (cluster size, SES) or individual level (e.g. age, sex) (Klar et al. 1995). This becomes particularly important if the distribution of these covariates, by bad luck, are not similarly distributed in the treatment and the control arms of the study. We will also explore the strength of possible effect modification by looking at the inference of multiplicative interaction terms discussed above. We will account for the fact that some children will have different total time at risk due to our definition of an episode discussed in Section D.3 by including an offset term in the regression models that is the natural log of the total time (in days) that a child was at risk of diarrhea. Finally, the regression model will return parameters that can be interpreted as the marginal ratio of diarrhea rates relative to the variable of interest. Specifically, the models will return an estimate of the ratio of diarrhea rates in populations that have the treatment versus those with the controls, all other factors (covariates) being equal in the two populations. If we find significant effect modification with treatment, then the model will return rate ratios specific to levels of the interacting variable(s), e.g., the ratio of rates in treatment versus control among populations with unsanitary facilities.

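### Villages are randomised within baseline-matched pairs, but the three analyses described have no stated primary and none names the pair or the baseline village rate

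*Protocol*

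**What the plan says.** **Design.** D.1 and D.6.b select 22 villages, measure diarrhoea for eight weeks and randomise within pairs: "Sites ranked by eight week baseline diarrhea rates are then grouped in pairs". The introduction to the revised application says that randomisation and matching "are the most effective ways to reduce the variance of our effect estimate". D.10 adds that simple random assignment cannot be relied on for comparability with 11 villages per arm.

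**Analysis.** The treatment comparison is described in four places:

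| Place | Method | Unit | Pair named? | Baseline village rate named? |
|---|---|---|---|---|
| A. Specific Aims: "Analysis will be conducted with mixed effects models adjusting for the clustered nature of the data" | mixed model | not stated | no | no |
| D.8, before Table 1 | mixed model, called more efficient | within-cluster data | no | no |
| D.9, comparison of rates: Pearson chi-square "test can be used to compare cluster or group level incidence rates" | cluster-adjusted chi-square | village | no | no |
| D.9, multivariate statistics: "we will report the inference based on robust estimates of the variance, we will assume the correlation within a cluster to be compound symmetry" | Poisson GEE | child | no | no |

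Covariate adjustment in D.9 is optional. The covariates it lists are cluster size, socio-economic status, age and sex. No method is designated primary.

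**The concern.** Randomisation within pairs restricts which allocations can occur. If baseline predicts follow-up, the arm difference varies less than it would under unrestricted allocation. A standard error computed from village-to-village spread within each arm does not see this and comes out too large. Separately, an uncorrected robust variance from 22 villages tends to come out too small. The two errors work in opposite directions, and their balance depends on a correlation that the protocol does not give.

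The trial is also open-label (E.8), and D.9 gives two different units of analysis for the same comparison. Leaving the choice among several unranked methods open until outcomes are known is an avoidable weakness.

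**Working it through.** **1. Inputs.** From D.8: "We consider a reduction of the annual incidence of 5 to 3.33 episodes per child <5" (rate ratio 0.667); "we require 80% power" at two-sided 5%; k = 0.2 for the final number, with k = 0.3 as the stated upper bound; 11 villages per arm; 30 children per village for 12 months. Assumed, because the documents do not give them: the correlation between a village's true baseline and follow-up rates (0 to 0.95), and child-level overdispersion (squared CV 0.5 unless stated).

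**2. The plan's own figure.** c = 2 + (1.96 + 0.84)² × {(R0 + R1)/y + k²(R0² + R1²)}/(R0 − R1)². With R0 = 5, R1 = 3.333, y = 10 and k = 0.2:

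2 + 7.84 × (0.833 + 1.444)/2.778 = 8.43, so 9 per arm. Adding 2 for village loss gives 11, which agrees with D.8. (The tables show 8.4 under a column headed k = 0.25; that label is a separate matter.) The formula has no matching term, so the planned size does not rely on the pairs.

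**3. Standard error by hand, k = 0.3, 30 child-years per village.**
- Variance of a log village rate ≈ k² + 1/(5 × 30) + 0.5/30 = 0.090 + 0.0067 + 0.0167 = 0.113.
- With no predictive baseline, the SD of the log rate ratio ≈ √(2 × 0.113/11) = 0.143. Simulation gives 0.143.
- The uncorrected robust variance divides by 11 instead of 10 in each arm: 0.143 × √(10/11) = 0.136. Simulation gives a mean of 0.134, so it is too small.
- At correlation 0.95 the simulated within-pair correlation of observed rates is about 0.56, so the true SD ≈ 0.143 × √(1 − 0.56) = 0.095. Simulation gives 0.094. The reported standard error still averages 0.136, and 0.136/0.094 = 1.45, about 45% too large.

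**4. Type I error at nominal 5%.** Simulation of 20,000 trials per setting: rank on the observed eight-week rate, pair, randomise within pairs, 22 villages. Ranges cover k = 0.2 to 0.3. The GEE is taken with an uncorrected robust variance and a normal reference.

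| Baseline/follow-up correlation | GEE, pairs ignored |
|---|---|
| 0 | 7.4–7.8% |
| 0.3 | 6.4–6.5% |
| 0.6 | 4.3–4.4% |
| 0.8 | 2.4–3.2% |
| 0.95 | 1.0–2.1% |

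Throughout, the paired t-test on log village rates gives 4.8–5.2% and the baseline-adjusted village regression 4.6–5.2%. A separate simulation gives 7.6–8.1% for the GEE at correlation 0 and 1.3–3.2% at 0.9, with the two matched analyses at 4.4–5.4%. With 18 villages at correlation 0, the GEE gives 7.7–8.4%.

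**5. Power.**
- Planned effect, k = 0.2: GEE 97–99%, paired 93–99%, baseline-adjusted 95–99.7%.
- Planned effect, k = 0.3: GEE 82–90%, paired 73–97%, baseline-adjusted 77–99%. The lower ends are at correlation 0, where the GEE figure is flattered by its inflated error.
- Rate ratio 0.75, k = 0.3, correlation 0.8: 57%, 67% and 72% in the same order. At correlation 0.9, in the separate simulation: about 62%, 76% and 81%.
- Rate ratio 0.75, k = 0.3, correlation 0: an unpaired village t-test gives 49.6%, paired 46.1%, baseline-adjusted 49.7%. This is the cost if matching achieves nothing.

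**The case against.** Much of the opposing case stands.

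- **Matching is not wasted.** A reader might infer that it is. The arms are still balanced and the true SD still falls (0.143 to 0.094 at k = 0.3). Only the credit in the reported inference is lost.
- **The error rate has no fixed direction.** A reader might infer inflation, or excess caution, as a certainty. The documents support neither, because the correlation is not given and the two errors nearly cancel at moderate values. Modelling details also matter: a run with child-level CV 0.5 gave 4.6% (k = 0.2) and 2.7% (k = 0.3) at correlation 0.9.
- **The normal reference is assumed.** D.9 states none. With a t reference on 20 df, the error at correlation 0 is 6.3–6.6%. A small-sample correction is commonly left to the SAP.
- **The chi-square is not an ever/never test.** Under a Poisson model 1 − e^(−5) = 99.3% and 1 − e^(−3.33) = 96.4% of children would have an episode, and a reader might conclude that the test is nearly uninformative. But D.5, D.6.c and D.9 define the outcome as episodes over person-time and apply the test to cluster rates, in permissive wording.
- **Adjustment for the baseline rate is not excluded.** The reference in D.9 to cluster-level baseline risk factors could cover it.
- **The methods are partly sequential.** D.9 can be read as simple comparisons followed by regression, and the sentence in A is a summary.

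What does not fall away is that the document itself gives differing methods and units for one comparison, ranks none, and nowhere ties the analysis to the matched randomisation. That is a conflict in the stated text, not detail left to an SAP.

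**Conclusion.** The point holds as an inconsistency between design and analysis: pair-matched randomisation, three unranked methods, and no named use of the pair or the baseline village rate. Under the assumed uncorrected GEE with a normal reference and 22 villages, type I error is about 8% at correlation 0, near 5% at about 0.5 to 0.7, and about 1–3% at 0.9. These figures rest on k = 0.2 to 0.3, an unstated correlation and an assumed child-level overdispersion. The planned effect remains well powered at k = 0.2. The loss of precision matters mainly near k = 0.3 or for effects smaller than planned. Severity: should fix.

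**What to change.** Name one primary analysis that respects the matching, and give the other as support:

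- regress log village incidence rate on arm and log eight-week baseline village rate, with a t reference on 22 − 3 = 19 df; or
- a paired t-test on the 11 within-pair log-rate differences, on 10 df.

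Village loss bears on the choice. D.8 allows for one to two lost villages per arm. Four losses in four different pairs would leave 7 pairs and 6 df for the paired test, while the regression would keep all 18 villages and 15 df.

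Keep the child-level GEE as secondary, with the baseline village rate as a covariate, a small-sample-corrected variance and a t reference. Bring the mixed-model statements in A and D.8 and the Pearson chi-square in D.9 into line with this, or mark them as supportive.

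**Cost.** Wording only, because the baseline survey is already planned. Against an unpaired comparison on 20 df, the regression gives up 1 df and the paired test 10. Power is slightly lower if baseline barely predicts follow-up, mainly for the paired test.

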#### **D.10. Critical assessment and possible limitations of the approach**

The randomized controlled trial is the most powerful and bias-free means for describing associations between interventions and outcome. This design provides the most accurate and critical evaluation of the efficacy of interventions. Accurate data on efficacy allow the calculation of the number of cases (or deaths) averted by an intervention in a given population. This then can be combined with the cost of implementation of SODIS to obtain cost effectiveness estimates.

Study Design: There is no ethical way to conduct this trial in a blinded fashion. We considered use of a cross-over study design, which would virtually remove any intra-person variation of diarrheal outcome due to factors other than the intervention. We are using such a design in our 1300 person water intervention study in Davenport, Iowa (Appendix G). Due to the substantial reduction in variability, sample size requirements would also be reduced. However, we abandoned this design option given the short trial period of 12 months as well as ethical reasons that object to the withdrawal of SODIS from households once begun in those households (i.e. crossover from active to placebo arm could not be justified). We compensate for this by the use of an amply large sample size in our proposed parallel arm design.

Study duration: One strength of the study compared to the one comprehensive study on the chlorination of drinking water (Quick et al. 1999) is the length of follow-up period of 12 months. In contrast to Quick *et al.* this will allow to measure seasonal effects of the SODIS intervention alongside with the seasonal infection patterns of agents causing diarrheal diseases such as rotavirus.

Sample size: Given the relatively large size of the study with 22 clusters and given that randomization will be employed at all levels we hope that residual bias will be measurable. While randomization of even small numbers of villages to intervention and non-intervention group ensures equal probability of assignment for each group, it cannot ensure that all potential sources of bias will be equally distributed. Pending our baseline field work in the trial villages, we have to anticipate a heterogeneity of the occurrence of baseline diarrheal diseases (our outcome) among the different village-clusters. A simple random assignment to the intervention or control group is unreliable to achieve baseline comparability among the study conditions. This applies particularly if the number of clusters in each condition is relatively small, as is in our study (N=11 villages). We thus, employ an *a priori* matching of the villages according to the baseline incidence of childhood diarrheal illness before random assignment of the intervention to one of the pairs.

Diarrheal episodes as outcome measure: Our outcome measure (diarrheal episodes) is subject to the influence of numerous measurable and unknown factors particularly in developing countries. By incorporating the suggestion made in the earlier review for *a priori* matching on the endpoint (baseline incidence of diarrhea) we have attempted to control for the effects of a number of unknown confounding factors as well as some of the factors that are difficult to assess such transient risk factors. We will be able to adjust for any relevant confounding factors that might randomly differ significantly in the groups.

